**Fig. 1 Fig1:**
[figure not shown]
Trial flowchart

### Inclusion and exclusion criteria

The trial will enrol patients affected by HIV-associated KS, requiring systemic therapy for KS. Patients will be required to be established on cART for HIV by at least 3 months, with CD4 count ≥ 100 cells/µL, and HIV-RNA < 200 copies/ml at screening. Patients are eligible independently from the previous exposure to chemotherapy for KS. Patients already exposed to immune-checkpoint inhibitors will be excluded.

The main inclusion and exclusion criteria are summarised in Table 2.

**Table 2 Tab2:** Summary of inclusion and exclusion criteria

**Inclusion Criteria**
1.Histologically proven diagnosis of Kaposi’s Sarcoma (KS) fulfilling the clinical criteria for cART-refractory disease: defined as KS with clinical progression or stable disease after at least 3 continuous months of combined anti-retroviral, with virological and immunological response (defined at 4) 2.Available pre-treatment biopsy 3.Established on cART for at least 3 months without adverse events (AEs) associated with cART > grade 1 by National Cancer Institute (NCI) Common Terminology Criteria for Adverse Events (CTCAE) criteria version (v.) 5.0. Note: modifications of cART during screening are allowed provided patients meet all other eligibility criteria and are on effective new regimen for at least 2 weeks 4.HIV viral load < 200 viral copies/ml and CD4 + T-cell count ≥ 100 cells/µL at screening 5.Measurable disease by modified AIDS Clinical Trial Group (ATCG) Kaposi sarcoma response criteria 6.Eastern Cooperative Oncology Group (ECOG) performance status of ≤ 2 7.Be of ≥ 18 years of age 8.Adequate haematological and organ function, defined as follows: -Absolute neutrophil count > 1.5 × 10 ꝰ/L -Platelet count > 100.000/mcL, -Haemoglobin > 90 g/L, -Total bilirubin ≤ 1.5 × upper limit of normal (ULN) or ≤ 2xULN for patients with Gilbert’s syndrome or on HIV protease inhibitors, -Aspartate aminotransferase (AST)/alanine aminotransferase (ALT) ≤ 2.5 × ULN (up to 5 × ULN if liver metastases are present), -Serum creatinine ≤ 2.5 × ULN or creatinine clearance (CrCl) > 60 ml/min in subjects with serum creatinine ≤ 1.5 × ULN. Calculation of CrCl should follow institutional standards -International normalized ratio (INR) or prothrombin time (PT) ≤ 1.5 × ULN unless patient is receiving anticoagulant therapy as long as PT or partial thromboplastin (PTT) is within therapeutic range of intended use of anticoagulants. Activated partial thromboplastin time (aPTT) ≤ 1.5 × ULN unless patient is receiving anticoagulant therapy as long as PT or PTT is within therapeutic range of intended use of anticoagulants 9.Female participants must have a negative serum pregnancy test within 72 h prior to taking study treatment if of childbearing potential and agree use a highly effective method of contraception from screening through 120 days after the last dose of study treatment or is of non-childbearing potential 10.Participant must agree to not breastfeed during the study or for 90 days after the last dose of study treatment 11.Male participant agrees to use a highly effective method of contraception (see Sect. 4.4 for a list of acceptable birth control methods) starting with the first dose of study treatment through 120 days after the last dose of study treatment. Note: Abstinence is acceptable if this is the established and preferred contraception for the patient 12.Participant receiving corticosteroids may continue as long as their dose is stable for least 4 weeks prior to initiating protocol therapy 13.Participant must be able to understand the study procedures and agree to participate in the study by providing written informed consent

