## Methods

### Trial design

The StarKap study is a single centre open label phase Ib trial assessing the safety, tolerability and preliminary efficacy of dostarlimab in patients affected by cART-refractory KS. The trial is sponsored by Imperial College London and is currently open to recruitment at Chelsea & Westminster Hospital, in London, UK.

A phase Ib, single-arm, open label study describing safety and tolerability of dostarlimab is necessary to answer the question of feasibility of anti-PD-1 immunotherapy in PLWH and KS. No dose-escalation was deemed necessary in this population due to the non-linear relationship between exposure and immune-mediated toxicity and the lack for dose-limiting toxicities observed in dose escalation studies of dostarlimab [15, 16].

The study will enrol 20 adult patients aged (aged ≥ 16 years) affected by HIV-related KS, fulfilling the criteria of cART-refractory KS. To this end, patients will be required to have KS that progressed or remained stable after at least 3 continous months of cART, with HIV-RNA < 200 copies/ml and CD4 count of at least 100 cell/µL at screening. Upon completion of screening procedures and confirmation of eligibility, patients will start treatment with dostarlimab within 28 days from screening. Dostarlimab will be administered intra-venously according to summary of product characteristics, at the dose of 500 mg every 3 weeks for the first 4 cycles and at 1000 mg every 6 weeks for the following cycles. Dostarlimab will be continued until completion of 1 year, loss of clinical benefit, inacceptable toxicities or withdrawal of consent, whichever comes first.

A safety lead-in phase will initially require a total of 6 patients, who will be observed for the emergence of dose-limiting-toxicities (DLTs) over a 21-days window from dosing. Following discussion within the trial steering committee it was opted to maintain a standard 21-days safety window for the first 6 subjects with a particular focus on the assessment of events of immune-reconstitution as well as qualitative and quantitative changes in parameters reflective of HIV control. The decision to enrol 6 subjects for the initial safety lead-in phase is in line with standard clinical trial design practice for early-phase trials. This number is generally considered sufficient to detect any early DLTs [17].

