**Exclusion criteria**
1.Receipt of anti-cancer therapy (chemotherapy, radiation therapy, immunotherapy or biologic therapy) including investigational therapy ≤ 4 weeks, or within a time interval less than at least 5 half-lives of the investigational agent, whichever is shorter, prior initiating protocol therapy. There should be no evidence of treatment-related adverse events > grade 1 CTCAE v.5 2.Major surgery within 3 weeks prior to initiating protocol therapy. Study participant must have recovered from any adverse events relating to surgery 3.Known active tuberculosis (TB) in the first 6 weeks of treatment 4.Known active Immune Reconstitution Inflammatory Syndrome (IRIS) related to opportunistic pathogens. Note: Patients with previous history of IRIS that has fully resolved at the time of screening are eligible 5.Known history of active uncontrolled hepatitis C virus (HCV) infection, defined as detectable plasma HCV RNA. Note: patients with positive HCV serology but negative HCV RNA or those successfully treated for HCV are eligible 6.Known history of active uncontrolled hepatitis B virus (HBV) infection, defined as detectable plasma HBV DNA in absence of therapy. Note: patients with HBV serology indicating immunization (i.e. positive hepatitis B surface antibody, HBsAb and negative core antibody HBcAb), patients with fully resolved acute HBV infection and those with chronic HBV infection adequately treated with antiviral therapy are eligible 7.Active auto immune disease that has required systemic treatment in the past 2 years (i.e. with use of disease modifying agents, corticosteroids or immunosuppressive drugs). Replacement therapy (eg. thyroxine, insulin, or physiologic corticosteroid replacement therapy for adrenal or pituitary insufficiency, etc.) is not considered a form of systemic treatment 8.History of idiopathic pulmonary fibrosis, organizing pneumonia, drug-induced pneumonitis, or idiopathic pneumonitis, or evidence of active pneumonitis on screening chest computed tomography scan 9.Prior therapy with anti-PD-1/PD-L1 and/or anti-CTLA-4 therapy either alone or in combination with other agents 10.Receipt of live vaccines within 30 days before the first dose of trial treatment and while participating in the trial; examples of live vaccines include, but are not limited to, the following: measles, mumps, rubella, chicken pox, yellow fever, seasonal flu, H1 N1 flu, rabies, bacillus Calmette-Guerin (BCG), and typhoid vaccine 11.Known hypersensitivity to dostarlimab components or excipients 12.Known psychiatric or substance abuse disorders that would interfere with cooperation with the requirements of the trial 13.Known additional malignancy that is progressing or requires active treatment. Exceptions include basal cell carcinoma of the skin or squamous cell carcinoma of the skin that has undergone potentially curative therapy or in situ cervical cancer 14.Participant has leptomeningeal disease, carcinomatous meningitis, symptomatic brain metastases, or radiologic signs of CNS hemorrhage 15.Systemic steroid therapy or any other form of immunosuppressive therapy that cannot be discontinued within 7 days prior to initiating protocol therapy

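### Minor eligibility wording errors: two minimum ages, a creatinine-clearance condition that never acts, and a steroid permission at odds with the steroid exclusion that leaves physiologic replacement unprotected

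*Protocol article*

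**What the plan says.** **Age.** Methods, Trial design: "The study will enrol 20 adult patients aged (aged ≥ 16 years". Table 2, inclusion 7: "Be of ≥ 18 years of age".

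**Renal function.** Table 2, inclusion 8: "Serum creatinine ≤ 2.5 × ULN or creatinine clearance (CrCl) > 60 ml/min in subjects with serum creatinine ≤ 1.5 × ULN", followed by the note "Calculation of CrCl should follow institutional standards". The bilirubin line of the same item has a similar two-part form: "Total bilirubin ≤ 1.5 × upper limit of normal (ULN) or ≤ 2xULN for patients with" Gilbert's syndrome or for those on HIV protease inhibitors.

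**Steroids.** Table 2, inclusion 12: "Participant receiving corticosteroids may continue as long as their dose is stable for least 4 weeks prior to initiating protocol therapy". Exclusion 15 bars "Systemic steroid therapy or any other form of immunosuppressive therapy that cannot be discontinued within 7 days prior to initiating protocol therapy". Within exclusion 7, which concerns autoimmune disease, the table adds that "physiologic corticosteroid replacement therapy for adrenal or pituitary insufficiency, etc.) is not considered a form of systemic treatment". Exclusion 15 has no such statement.

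**The concern.** These are operative rules for who may receive a PD-1 inhibitor, and the Trial design section says that the trial is already recruiting. Each of the three has a different fault:

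- The two ages contradict each other.
- The renal rule contains a test that cannot alter any decision, although staff are told how to calculate it.
- The steroid permission and the steroid exclusion point in opposite directions for one kind of patient, and the one exemption that would help sits in a different criterion.

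What is at stake is consistent screening. A patient on necessary hormone replacement could be turned away without reason. If inclusion 12 were taken as decisive, a patient on a stable immunosuppressive dose could be let in, although the trial's rationale is to restore CD8+ T-cell function.

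**Working it through.** The plan gives no figure to reproduce here, so the check is logical. All inputs are the printed rules cited above.

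**Age.** The limits are 16 (Trial design) and 18 (Table 2). They give different answers only for patients aged 16 or 17, who are eligible under the first and ineligible under the second. The word 'adult' in the Trial design sentence and the entry in Table 2 both point to 18.

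**Renal.** Let A be creatinine ≤ 2.5 × ULN, B be clearance > 60 ml/min, and C be creatinine ≤ 1.5 × ULN. The rule is A or (B and C). Since 1.5 < 2.5, C lies inside A, so (B and C) lies inside A and the rule reduces to A.

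- Grid check: creatinine 0.50 to 4.00 × ULN in steps of 0.01 (351 values) by clearance 5 to 150 ml/min in steps of 1 (146 values) gives 351 × 146 = 51,246 combinations. Removing the clearance limb changes eligibility in 0 of them.
- Alternative grammar: if the 1.5 × ULN qualifier governs the whole sentence, the rule is (A or B) and C. This reduces to C, and clearance again changes 0 combinations.
- Reading 'or' as 'and', so that clearance is required only of those at or below 1.5 × ULN, does not rescue it. A patient at 1.4 × ULN with clearance 50 would fail, while one at 2.4 × ULN with clearance 20 would pass.
- A form that does act, for illustration only: creatinine ≤ 1.5 × ULN, or clearance > 60 when creatinine is above 1.5 × ULN. The clearance limb then changes 250 × 90 = 22,500 of the 51,246 combinations. Grid counts show only whether a limb acts; they are not proportions of patients.
- Comparison with bilirubin: at 1.8 × ULN, a patient with Gilbert's syndrome passes, and a patient with neither that syndrome nor a protease inhibitor fails. That second limb works because it admits a group that fails the first limit. The renal limb names a group that has already passed.

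**Steroids.** For systemic corticosteroids:

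| Dose stable 4 weeks | Can be stopped within 7 days | Inclusion 12 lets it continue | Exclusion 15 bars patient | Opposed |
|---|---|---|---|---|
| No | No | No | Yes | No |
| No | Yes | No | No | No |
| Yes | No | Yes | Yes | **Yes** |
| Yes | Yes | Yes | No | No |

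One of the four cells is opposed. Non-systemic steroids never meet exclusion 15, so none of their four cells is. In the opposed cell, the usual practice is that a patient must meet every inclusion and no exclusion, so exclusion 15 decides and the patient is out.

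Physiologic replacement falls in the same cell, on the assumption that replacement for adrenal or pituitary insufficiency cannot simply be stopped. Inclusion 12 lets it continue. Exclusion 7 says that it does not count as systemic treatment, but only for the purpose of that item. Exclusion 15, read as printed, bars it.

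**The case against.** The strongest defence has four parts.

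1. Exclusions prevail over a permissive inclusion, so the steroid rules do give an answer. Inclusion 12 keeps a role for topical or inhaled products, because it says corticosteroids where exclusion 15 says systemic. This stands in large part. A reader might infer that the two criteria are irreconcilable; the document does not support that. What remains is that inclusion 12 states no route, and so misleads for systemic doses, and that replacement is exempted in one criterion and not in the other. Carrying the exemption from exclusion 7 to exclusion 15 is a natural reading, but it is not a stated one.

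2. The age of 16 is a slip in a garbled phrase. Agreed. A reader might infer that the age rule in Table 2 is wrong; it is not, and only the Trial design text needs correction.

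3. The renal rule still yields one definite answer, creatinine ≤ 2.5 × ULN. Also agreed: as printed, it misclassifies nobody against its own text. A reader might infer that a particular stricter threshold was meant. The document does not show which, although the calculation note suggests that clearance was meant to count.

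4. Table 2 is a summary and the full protocol is not shown. This weakens the steroid limb most, since qualifiers on route may stand there. It does not account for two different ages, or for a printed condition that cannot act.

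A reader might also put a size on this by noting that one patient in 20 is 5 percentage points of the adverse-event percentages. That is the weight of any patient in a 20-patient trial, not an effect of these rules, and should not be used as their magnitude.

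**Conclusion.** The point holds as a minor one: three statements are wrong or misleading as written.

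- **Age:** a plain contradiction, confined to 16- and 17-year-olds.
- **Renal:** clearance never affects eligibility. On the natural reading of the sentence, a patient at 2.4 × ULN qualifies at any clearance.
- **Steroids:** assuming that exclusions prevail, inclusion 12 misleads for systemic doses, and physiologic replacement lacks the protection that exclusion 7 gives it elsewhere.

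Confidence is high for age and renal. It is lower for steroids, where the conclusion depends on not carrying the exemption across criteria. The document does not say how many patients any of these rules would touch, and the number may be zero. No sample size, error rate or analysis is altered.

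**What to change.** 1. In the Trial design section, change the minimum age to 18, in line with Table 2.
2. In inclusion 8, the sponsor should restore the intended cut-offs so that the clearance condition applies to patients whom the first limb does not already admit. Otherwise, delete the clearance limb together with its calculation note.
3. Limit inclusion 12 to non-systemic (for example topical or inhaled) or physiologic replacement corticosteroids, and repeat the replacement exemption of exclusion 7 in exclusion 15.

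The cost is a wording change in one sentence and in Table 2. Eligibility may become slightly narrower if a working clearance condition is restored. If the full protocol already has the right wording, only the article needs correcting.

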**Exclusion criteria**
1.Receipt of anti-cancer therapy (chemotherapy, radiation therapy, immunotherapy or biologic therapy) including investigational therapy ≤ 4 weeks, or within a time interval less than at least 5 half-lives of the investigational agent, whichever is shorter, prior initiating protocol therapy. There should be no evidence of treatment-related adverse events > grade 1 CTCAE v.5 2.Major surgery within 3 weeks prior to initiating protocol therapy. Study participant must have recovered from any adverse events relating to surgery 3.Known active tuberculosis (TB) in the first 6 weeks of treatment 4.Known active Immune Reconstitution Inflammatory Syndrome (IRIS) related to opportunistic pathogens. Note: Patients with previous history of IRIS that has fully resolved at the time of screening are eligible 5.Known history of active uncontrolled hepatitis C virus (HCV) infection, defined as detectable plasma HCV RNA. Note: patients with positive HCV serology but negative HCV RNA or those successfully treated for HCV are eligible 6.Known history of active uncontrolled hepatitis B virus (HBV) infection, defined as detectable plasma HBV DNA in absence of therapy. Note: patients with HBV serology indicating immunization (i.e. positive hepatitis B surface antibody, HBsAb and negative core antibody HBcAb), patients with fully resolved acute HBV infection and those with chronic HBV infection adequately treated with antiviral therapy are eligible 7.Active auto immune disease that has required systemic treatment in the past 2 years (i.e. with use of disease modifying agents, corticosteroids or immunosuppressive drugs). Replacement therapy (eg. thyroxine, insulin, or physiologic corticosteroid replacement therapy for adrenal or pituitary insufficiency, etc.) is not considered a form of systemic treatment 8.History of idiopathic pulmonary fibrosis, organizing pneumonia, drug-induced pneumonitis, or idiopathic pneumonitis, or evidence of active pneumonitis on screening chest computed tomography scan 9.Prior therapy with anti-PD-1/PD-L1 and/or anti-CTLA-4 therapy either alone or in combination with other agents 10.Receipt of live vaccines within 30 days before the first dose of trial treatment and while participating in the trial; examples of live vaccines include, but are not limited to, the following: measles, mumps, rubella, chicken pox, yellow fever, seasonal flu, H1 N1 flu, rabies, bacillus Calmette-Guerin (BCG), and typhoid vaccine 11.Known hypersensitivity to dostarlimab components or excipients 12.Known psychiatric or substance abuse disorders that would interfere with cooperation with the requirements of the trial 13.Known additional malignancy that is progressing or requires active treatment. Exceptions include basal cell carcinoma of the skin or squamous cell carcinoma of the skin that has undergone potentially curative therapy or in situ cervical cancer 14.Participant has leptomeningeal disease, carcinomatous meningitis, symptomatic brain metastases, or radiologic signs of CNS hemorrhage 15.Systemic steroid therapy or any other form of immunosuppressive therapy that cannot be discontinued within 7 days prior to initiating protocol therapy

## Objectives and endpoints

The main objective of the StarKap trial is to test the safety and the tolerability of dostarlimab in patients affected by cART-refractory KS. Efficacy is the secondary objective of the study. Along with the clinical objectives, we have designed and planned a set of translational objectives to identify the immunological correlates of response to dostarlimab in cART-refractory Kaposi’s sarcoma. Table 3 summarises the objectives and endpoints of the study.

**Table 3 Tab3:** Trial Objectives and endpoints

Objective	Endpoint
**Primary**	
To determine the safety and tolerability of dostarlimab in cART-refractory HIV associated Kaposi Sarcoma	Incidence of adverse events measured by NCI CTC criteria v.5.0 up to 90 days after treatment cessation
**Secondary**	
A) To characterize the efficacy of dostarlimab in cART-refractory HIV associated Kaposi Sarcoma	1. Objective Response rate (ORR) evaluated at week 10 and week 31 (± 7 days) and end of treatment by modified AIDS Clinical Trial Group (ACTG) Kaposi sarcoma (KS) response criteria. For patients with visceral involvement Response Evaluation Criteria In Solid Tumours (RECIST) v1.1 will be used to complement modified ACTG response criteria 2. Progression free survival (PFS) from screening 3. Time to progression from the first evidence of documented objective response to dostarlimab
**Exploratory**	
A) To identify immunological correlates of response to dostarlimab in cART-refractory HIV associated Kaposi Sarcoma B) To define the impact of microbiome composition on response to dostarlimab C) To assess quality of life in the study population	1. Assessment of the phenotype of intra-tumour and peripheral immune cells at different timepoints and to correlated with ORR 2. Assessment of the transcriptional profile of intra-tumoral immune cells at different timepoints and to correlate with ORR 3. The dynamic changes of anti HHV-8 T cells response during treatment 4. The differences in the baseline microbiome composition according to ORR 5. To evaluate the changes in quality of life parameters during treatment

### Translational investigational plan

The hypothesis that guides the translational biomarker plan associated with StarKap trial is centred on the role of effector tumour infiltrating T-cell as a mechanism underscoring disease-modulating activity from immunotherapy in KS. We hypothesise dostarlimab to elicit anti-tumoral response by reinvigorating the T-cells effector function within the tumour microenvironment. To this end, tumour, bloods and stools samples will be longitudinally collected.A) Tumour samplesTumour biopsy will be mandatory at screening. Optional tumour samples will be collected at cycle and at the end of treatment to characterise the phenotype and the transcriptional profile of the intra-tumoral immune infiltrate.The phenotype of the intra-tumoral immune system will be assessed by performing imaging mass cytometry using a pre-defined panel of 30 markers specific for both the innate and adaptive immune system. The relative expression of the markers of interest will be evaluated pairwise in pre-on treatment samples and analysed in relationship with response to treatment.Transcriptomic profiling will be conducted in parallel with imaging mass cytometry experiments on tumour samples. Patients with a partial response will be categorised as “responders,” while those with stable or progressive disease will be classified as “non-responders.” Pathway enrichment analysis and immune deconvolution analysis will be conducted comparatively between the two groups. The same comparisons will be performed between pre-treatment and on-treatment samples.Available evidence suggest that HHV-8 specific T cells response is pivotal to prevent KS development. To verify whether immunotherapy elicits anti-tumour response by inducing clonal T-cells expansion, we will perform targeted sequencing of the rearranged VDJ segments on the CDR3 region of the TCRBeta chain on DNA extracted from FFPE pre-treatment and on-treatment tumour samples.B) Bloods samplesExtra bloods samples will be collected at screening, cycle 4, cycle 8 and end of treatment.We will characterize baseline immune phenotype of PBMC and their changes during treatment using multi- parameter flow-cytometry. Mean and median values of the diverse immune cell populations detected by flow-cytometry will be measured and compared across timepoints, and between responders and non-responders.To investigate whether response to immunotherapy is associated with specific immune-response, we will perform targeted sequencing of the rearranged VDJ segments on the CDR3 region of the TCRBeta chain on DNA extracted T-cell receptor beta- chain (TCRB) repertoire in peripheral blood lymphocytes to assess for dynamic changes in clonality of the T- cell response.To assess whether response to anti PD-1 (defined as reported in the clinical objectives) is associated with a reduction in HHV-8 viral replication and increased immune response against HHV-8 we will evaluate the changes in HHV-8 DNA level by real-time PCR from whole blood samples at baseline, cycles 4, cycle 8 and at the EOT.To confirm determine if response to KS is associated with increase T-cells response against HHV-8, we will perform ex-vivo T-cells stimulation with a pool of overlapping peptides spanning selected HHV-8 reading frames (ORF) and assess the immune response using interferon gamma assay.C) Stools samplesThe functional interaction between commensal bacteria and host immune system has been widely recognized in humans and animal models [18]. HIV infection has been reported to alter the composition of the intra-mucosal T cells with consequent alteration of the intestinal barrier permeability and increased translocation of bacterial products into the blood stream [19]. Furthermore, the presence of alterations within the intestinal immune environment, has been reported to alter the composition of the gut microbiome in people living with HIV, and this has been associated with persistent chronic inflammation and peripheral T cells activation [20]. At the same time, the lack of microbiome diversity and the enrichment of specific taxa of commensal bacteria including Bifidobacteria, Akkermansia and Ruminococcaceae has been associated with reduced responsiveness to immunotherapy in patients with advanced malignancies through a direct effect of gut microbiome products on peripheral and intra-tumoral immune cells [21].To verify if the composition of the stool microbiome correlates with intra-tumoral and peripheral immune cells phenotype, and with response to dostarlimab, we will longitudinally characterize gut microbiome by sequencing hypervariable V1-V2 region of 16S rRNA gene from stool DNA collected at baseline.

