**Methods:**

The trial will enrol 20 patients in total. After completion of the screening procedures, participants will receive the first dose of dostarlimab within 28 days. Dostarlimab will be administered at the dose of 500 mg evry 3 weeks for the first 5 cycles, and at 1000 mg every 6 weeks thereafter. Treatment will continue until disease progression, unacceptable toxicity, or completion of 1 year of treatment. The first 6 patients will be enrolled in a safety-lead-in phase, if no dose-limiting toxicities (DLTs) will occur within the 21 days in the first 6 participants, trial will continue. Patients will be monitored for the emergence of adverse events until 90 days after the last dose of treatment. Tumour response will be assessed as objective response rate (ORR) at cycle 4, cycle 8 and end of treatment. Tissue, bloods, and stool samples will be collected at baseline, on treatment and at end of treatment to satisfy the related translation plan.

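### The responder rule for tumour transcriptomics assigns partial response, stable disease and progressive disease but leaves complete response in neither group, out of line with the ORR-based endpoint it serves

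*Protocol article*

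**What the plan says.** The rule is in the Translational investigational plan, part A (tumour samples), in the text on transcriptomic profiling. It reads "Patients with a partial response will be categorised as" responders, "while those with stable or progressive disease will be classified as" non-responders. The next sentence puts the labels to use: "Pathway enrichment analysis and immune deconvolution analysis will be conducted comparatively between the two groups".

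Part B (blood samples) refers to response in two ways that matter here. Flow-cytometry values are to be "compared across timepoints, and between responders and non-responders", with no definition of those labels. The HHV-8 DNA analysis instead rests on "response to anti PD-1 (defined as reported in the clinical objectives").

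In Table 3, the second exploratory endpoint is "Assessment of the transcriptional profile of intra-tumoral immune cells at different timepoints and to correlate with ORR". The ORR itself is a secondary endpoint in the same table, assessed "by modified AIDS Clinical Trial Group (ACTG) Kaposi sarcoma (KS) response criteria" and complemented by RECIST v1.1 where there is visceral disease.

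**The concern.** A rule that divides patients into two groups should place every patient whose response has been assessed. This one names three of the four usual response categories and omits the best one. A statistician following it has two options for a complete responder: leave the patient out, or choose a group when the case arises, possibly with the expression data already in view.

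Neither option suits the purpose. The stated exploratory objective is to find immunological correlates of response, and the Conclusions section says the trial will describe depth of response. A complete responder is the most informative patient for both. The omission also means that the same patient could count as a responder in the HHV-8 DNA analysis and have no group in the transcriptomic one, although both are meant to bear on the same question.

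**Working it through.** The plan states no figure to reproduce. The check has two parts: whether the rule covers all categories and agrees with the rest of the article, and how many patients the gap could involve.

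**Coverage and consistency**

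| Analysis | How response is defined | Where a complete responder goes |
|---|---|---|
| Tumour transcriptomics (pathway enrichment, immune deconvolution) | Partial response against stable or progressive disease | Neither group |
| Blood flow cytometry | Responder labels only, not redefined | Neither group, if the tumour definition carries over |
| Blood HHV-8 DNA | Response as in the clinical objectives | Responder |
| Exploratory endpoint 2, Table 3 (transcriptional profile) | ORR | Responder |
| Exploratory endpoint 4, Table 3 (baseline microbiome) | ORR | Responder |

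The last three rows assume that ORR means complete plus partial response. That is the convention, but the article does not spell it out. Rows 1 and 4 concern the same analysis, and they disagree.

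**Possible size**

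Inputs from the article: 20 patients (Abstract, Methods). The Rationale gives two reference ORRs by ACTG criteria in HIV-associated Kaposi sarcoma: 40% (nivolumab subgroup) and 62.1% (pembrolizumab). Assumed input: a complete-response rate c of 5% to 15%, because the article gives none.

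- Expected complete responders = 20 × c: 1 at 5%, 2 at 10%, 3 at 15%.
- Chance of at least one among 20 = 1 − (1 − c)^20: 0.64 at 5%, 0.88 at 10%, 0.96 at 15%. At a rate of only 2% it is 0.33.
- Expected objective responders = 20 × ORR: 20 × 0.40 = 8.0 and 20 × 0.621 = 12.4.
- Share of objective responders left unclassified = c / ORR:

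| Assumed c | ORR 40% | ORR 62.1% |
|---|---|---|
| 5% | 1/8.0 = 12.5% | 1/12.4 = 8% |
| 10% | 2/8.0 = 25% | 2/12.4 = 16% |
| 15% | 3/8.0 = 37.5% | 3/12.4 = 24% |

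With complete response added to the responder group, the unclassified number is zero at every assumed rate.

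**The case against.** The strongest reply is that this is a drafting slip for at least a partial response. No sentence says that complete responders will be removed, and the surrounding text points to the ordinary meaning: Table 3 ties the profile to ORR, and the HHV-8 analysis refers back to the clinical objectives. That is plausible, but nothing in the article confirms it. This is also not a detail left to a fuller document. The article chose to state the rule, and the rule as stated is incomplete.

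Other parts of the reply limit the point, and they stand:

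- **Scope.** A reader might infer that every biomarker analysis loses its complete responders, or that tumour and blood results in general cannot be compared. The text does not support this. Imaging mass cytometry is related to response without this rule, the microbiome endpoint uses ORR, and in the blood section the explicit conflict is confined to HHV-8 DNA. Flow cytometry is affected only if it inherits the tumour definition.
- **Timing.** A reader might also object that no assessment is named for classifying patients, although response is read at three times. For an exploratory analysis this is commonly left to the full protocol or analysis plan, neither of which is shown, so it is not an error here.
- **Size.** The complete-response rates are assumed, and 37.5% pairs the highest assumed rate with the lower reference ORR. The base of 20 is also a ceiling: this section makes on-treatment and end-of-treatment tumour samples optional, so the number affected in paired comparisons is unknown.
- **Power.** The trial makes no power calculation for hypothesis testing, so an argument from lost power carries little weight.

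**Conclusion.** The point holds for the comparison to which the rule is attached. As written, complete responders belong to neither group in pathway enrichment and immune deconvolution, and possibly in the flow-cytometry comparison. The rule does not implement the ORR-based endpoint in Table 3 and differs from the HHV-8 DNA definition.

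The omission of complete response is plain from the text. The size is not known: about 1 to 3 of 20 patients if the complete-response rate is 5% to 15%, which is 8% to 37.5% of objective responders at the two reference ORRs. The mismatch with ORR rests on the conventional meaning of objective response.

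The consequence is confined to exploratory work. The primary safety endpoint, the ORR and progression-free survival analyses, and the conduct of the trial are untouched.

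**What to change.** Replace the rule with one sentence: responders are patients with a complete or partial response, and non-responders are patients with stable or progressive disease, by the modified ACTG criteria complemented by RECIST v1.1 for visceral disease, as for the ORR endpoint. State that this single definition applies wherever a translational analysis compares responders with non-responders, so that the flow-cytometry labels are covered as well.

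The correction need not go further. In particular, it should not count patients without an evaluable response as non-responders. The Statistical analysis section limits the efficacy population to treated patients who undergo efficacy evaluation, and adding patients of unknown response could blur a biological contrast.

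The cost is a wording change, with no new patients, samples or assays. It is best made before the biomarker data are linked to response.
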